## Abstract

**Background:**

While almost half of older adults admitted to hospital are prescribed potentially inappropriate medicines, less than 1% have a medicine proactively deprescribed during admission in the UK. The CompreHensive geriAtRician-led MEdication Review (CHARMER) intervention is designed to address geriatricians’ and pharmacists’ barriers and enablers to deprescribing. The CHARMER definitive trial will evaluate effectiveness, cost-effectiveness and safety.

**Methods:**

A stepped-wedge cluster randomised controlled trial will be conducted in 20 hospitals in England, with four hospitals in reserve. All hospitals will collect baseline data. Every 3 months, five hospitals will be randomised to receive the intervention. The intervention, implemented by a local project manager, comprises a hospital action plan to set deprescribing as an organisational goal; workshops for pharmacists and geriatricians to change beliefs about deprescribing; weekly briefings between geriatricians and pharmacists to discuss opportunities for deprescribing; benchmarking reports to compare deprescribing performance across participating hospitals. With an average of 200 patients admitted and discharged during each step, the study will have 89.5% power at 5% significance level and intra-class correlation coefficient of 0.05 to detect a 3% difference in 90-day re-admission rate from 16.7% versus 13.7%. Anonymised routinely collected data, including readmissions, will be obtained for all patients admitted during the study period. Enhanced data collection periods of 1 month during control and intervention periods will be used to recruit patients and data for secondary outcomes and process evaluation.

**Discussion:**

A stepped-wedge design enabled a smaller number of hospitals and patients to be included than a traditional cluster-randomised design. The complexity of intervention implementation necessitated a project manager in addition to the principal investigator responsible for trial conduct. Using routinely collected data for the primary outcome measure should ensure that the trial has sufficient power on completion. Planned enhanced data collection for short periods of time improves trial efficiency.

**Trial registration number:**

ISRCTN13248281.

STRENGTHS AND LIMITATIONS OF THIS STUDYCluster-randomised stepped-wedge design trial.Large multi-site hospital-based deprescribing trial in older person’s setting.Feasibility-tested trial and theory-informed intervention.Collation of primary outcome measure for all patients recruited onto the ward to optimise likelihood of achieving target sample size.Enhanced data collection period to obtain secondary outcome data and inform process evaluation.

## Introduction

### Background and rationale

 The WHO Global Patient Safety Challenge: Medication Without Harm aims to reduce severe avoidable medication-related harm by 50%.^1^ Polypharmacy, as a risk factor for both patient harm^2^ and death,^3^ is recognised as a ‘key action area’ by the WHO.^1^ A UK national review of prescribing in 2021 recognised the significant extent of overprescribing and recommended several primary care-based interventions to address this.^4^ A meta-analysis of deprescribing interventions in primary care identified a small reduction in all-cause mortality, thereby justifying the recommendation.^5^

While it is estimated that half of older people at the point of entering hospital are already prescribed at least one medicine which may be potentially inappropriate,^6^ very few are stopped during admission in the UK.^7^ When deprescribing does occur, it is usually in response to presenting harm, that is, it is reactive rather than proactive.^7^ An opportunity to reduce overprescribing in hospital through proactive deprescribing is therefore being missed and may supplement similar activities in primary care. Hospital deprescribing trials have historically focused on process measures such as reduction in the proportion of potentially inappropriate medicines, rather than meaningful clinical outcomes.^8^

A lack of focus on addressing the barriers and enablers to deprescribing in hospitals when developing interventions may explain the lack of efficacy reported in existing deprescribing trials.^8 9^ We have used behaviour change theory to underpin the development of an intervention that is designed to address geriatricians’ and pharmacists’ capability, opportunity and motivation to identify opportunities to deprescribe and initiate deprescribing discussions with older people. Combined with extensive co-design work with the target audiences,^10^ our approach may enhance the likelihood of good implementation fidelity and resulting effectiveness.^11^

We developed the CompreHensive geriAtRician-led MEdication Review (CHARMER) deprescribing intervention using evidence regarding the barriers and enablers to deprescribing and behaviour change theory.^10 12 13^ CHARMER aims to facilitate geriatricians and pharmacists to identify opportunities for proactive deprescribing and initiate deprescribing conversations with older adults in hospital. The intervention comprises five components:

A hospital action plan to set deprescribing as an organisational goal to be achieved by implementing the remainder of the CHARMER intervention components.A geriatrician workshop with pre-prepared videos of peers navigating challenging deprescribing discussions with patients and relatives.A pharmacist workshop with case studies to address negative beliefs about the consequences of deprescribing.Weekly pharmacist and geriatrician briefings to identify opportunities for proactive deprescribing.Weekly benchmarking reports on deprescribing activities to allow sites to compare their performance against other sites.

In line with the UK Medical Research Council guidance for developing and evaluating complex interventions,^14^ the CHARMER intervention and trial design were feasibility tested.^15^ This led to numerous changes to both intervention implementation support and trial design, with the most significant being the decision to move from a cluster RCT to a cluster randomised stepped-wedge design. Due to the increase in power associated with a stepped-wedge design, this change requires half the number of hospitals for the trial representing more efficient trial design and thus better value for money. Furthermore, this design provides longer term follow-up data in a proportion of intervention hospitals and will thereby allow us to assess whether the intervention is normalised.

### Objectives

To describe the design of the definitive trial of the CHARMER hospital deprescribing intervention to evaluate its effectiveness, cost-effectiveness and safety.

### Trial design

Cluster randomised stepped-wedge design trial with internal pilot. A maximum of 24 hospitals (20 active, four reserve) across England will be recruited to take part. All participating hospitals will begin the trial at the same time in a control phase.

We will step hospital sites into the intervention ‘implementation phase’ at 3 month intervals (five hospitals every 3 months in four steps). The intervention ‘implementation phase’ will last for 3 months for all hospitals, prior to transferring into the active intervention phase. Each site will therefore take part in the trial for a total of 18 months (with an additional 3-month follow-up period for data collection). This is summarised in figure 1.

**Figure 1 F1:**
[figure not shown]
Schedule of enrolment, consent, intervention and data collection.

To ensure effective implementation of the intervention, a Project Manager is required at each site. This will usually be in addition to the Principal Investigator (PI), who is responsible for research delivery. Where capacity allows, the PI will be allowed to additionally assume the role of Project Manager.

Outlined here is the protocol for the main trial. Process evaluation protocol and results papers will be published separately.

## Methods: participants, interventions and outcomes

Methods outlined below based on Protocol V.1.1 2023. The trial is registered with ISRCTN Registry 13 248 281 University of Leicester ([contact]) acted as sponsor for the trial. They took no active involvement in either the management or delivery of the trial.

### Patient and public involvement

A patient and public involvement (PPI) group consisting of older adults experiencing polypharmacy (n=3) and family members/carers (n=2) are core members of the CHARMER research team. Our PPI group has contributed to the development and design of this trial, including developing the protocol, reviewing and editing participant information sheets and consent forms to ensure readability, and commenting on qualitative topic guide content. PPI group members attend weekly trial management meetings and will support the research team in the analysis, write-up and dissemination of the study findings.

### Trial setting

Acute hospitals in England with care of the older wards.

### Eligibility criteria

Proposed inclusion and exclusion criteria for hospitals, practitioners and patients are:

### Hospitals

Inclusion

Acute hospital.Provide an older people’s medicine service with at least one inpatient ward on which to conduct the CHARMER trial (the study ward).The majority of patients on the study ward(s) have a minimum length of stay of 3 days.The average total monthly throughput across study ward(s) of approximately 100 patients has at least one geriatrician (consultant or specialist registrar) and at least one ward-based pharmacist working on them.There is an electronic prescribing system on the study ward(s).The hospital is willing and has the capability and capacity to implement the five components of the CHARMER intervention.Able to provide a 0.2 whole time equivalent Project Manager to oversee implementation of the CHARMER intervention over a 14-week period (3 month implementation phase and 2 weeks within the active intervention phase).Named clinician willing and appropriate to take PI responsibility.Suitably trained staff, for example, sufficient research nurses, to recruit patient and personal consultee participants and enter required data.

Exclusion

Wards that primarily host patients who are medically fit for discharge and awaiting discharge care packages.Hospitals without a ward-based pharmacy service.Mental health hospitals.Hospitals that implemented the intervention in the feasibility study.

### Practitioners

Inclusion criteria:

Consultant geriatrician or specialist registrar and appropriately qualified pharmacists working across Older People’s Medicine wards.

Exclusion criteria:

Less than 0.3 whole time equivalent of ward-based time for pharmacists.

### Who will take informed consent?

Hospitals will be recruited to participate through the National Institute for Health and Care Research (NIHR) Research Delivery Network (RDN) in England.^16^ Funding to incentivise participation within hospitals is provided nationally and based on the number of enrolled patients. Consent for geriatricians and pharmacists to participate will be taken by the central research team within the Norwich Clinical Trials Unit (NCTU).

Consent for patients to provide non-routinely collected data for the enhanced data collection periods will be undertaken by local research nurses or members of the healthcare team with the relevant training in obtaining informed consent for research purposes. These individuals will usually be employed by the RDN. Any patients deemed inappropriate by the research nurses or members of the healthcare team, such as those lacking capacity or near end of life, will not be consented.

### Interventions

#### Explanation for the choice of comparators

The control steps will consist of the provision of usual care for older people admitted to participating older people’s medicine wards.

#### Intervention description

The intervention is summarised in the background and described in detail in a separate publication.^10^ The action plan and geriatrician and pharmacist workshops will be delivered during the 3-month implementation phase. The weekly briefings and benchmarking reports will occur throughout the active intervention phase.

#### Criteria for discontinuing or modifying allocated interventions

There are no plans to discontinue or modify any elements of the intervention as the trial progresses.

#### Strategies to improve adherence to the intervention

The intervention will be delivered to geriatricians and pharmacists (the target audience) and not patients. The Project Managers have been employed to ensure that the intervention is implemented as intended and in alignment with the Trust’s standard procedures. Once the trial is complete, hospitals and participating practitioners can decide whether they wish to continue with the intervention.

#### Relevant concomitant care permitted or prohibited during the trial

The intervention is focused on healthcare professionals with an increase in deprescribing discussions and activity an anticipated outcome. Patients will continue to receive all types of concomitant care during the trial with nothing prohibited.

#### Provisions for post-trial care

There are no provisions for post-trial care. Communication of any medicines deprescribed to primary care physicians will be undertaken as part of standard care at time of hospital discharge.

### Outcomes

Selection of outcome measures was based on a previously developed core outcome set designed for hospital-based deprescribing interventions.^17^ The primary outcome measure was selected as hospital readmission within 90 days as this was considered to be sufficiently sensitive and proximal to the intervention.

Outcome data are summarised in table 1. Costs and resource use, as well as economic outcomes, will be captured via expert opinion and review of study records where relevant.

**Table 1 T1:** Outcome data

Routinely collected data (without consent)	When	How
Mortality for any reason	90 data post-discharge	Hospital records and NHS England* Office of National Statistics Mortality records
Number of hospital stays†	90 data post-discharge	Hospital records and NHS England* Hospital Episode Statistics Admitted patient care
Number of planned and unplanned admissions and readmissions for treatment or monitoring of health†		

Intensive data collection (with consent)¶	When	How
Satisfaction with deprescribing process‡	2 weeks post-discharge	Postal questionnaire
Adverse drug events§	90 days post-discharge	Telephone questionnaire
Health-related quality of life (EQ-5D-5L††)^23^	Pre-discharge 90 days post-discharge	Face to face on ward Telephone questionnaire
Primary care consultations†	90 days post-discharge	Telephone questionnaire
Community pharmacy dispensed medicines†	90 days post-discharge	NHS England*
Number of ‘Regularly’ prescribed medicines	On admission and discharge	Routine hospital records^**^
Number of ‘As required’ prescribed medicines		
Number of medicines prescribed on admission which are stopped during admission while on study ward		
Number of medicines prescribed on admission with dosage reduced during admission while on study ward		
Number of stopped medicines prescribed on admission which are stopped during admission while on study ward and then restarted		

* National agency responsible for collation and provision of healthcare data.

† Captured for additional health economic analysis purposes.

‡ Questionnaire with 12 items based on previously published survey tool.^25^

§ Questionnaire with 17 items inviting respondents to indicate whether or not they have experienced any of the medication-related adverse events listed. The list is derived from an observational study of medication-related adverse events.^26^

¶ During enhanced data collection periods, consent/assent for routine data collection was sought wherever possible, but where not possible, Section 251 approval was applied. Where participants declined to consent/assent, routine data was not collected.

** To enable the outcomes regarding medication to be collated the following data will be collected: Name, dose and frequency of all medicines prescribed to the patient before any changes were made during the hospital admission. Any changes made to the above medicines (stopped, dose reduction, dose increase or change in frequency). Name, dose and frequency of any new medicines started during the admission that are requested to be continued post discharge.

†† EQ-5D-5L, EuroQol 5-Dimension 5-Level.

NHS, National Health Service.

Geriatrician and pharmacist participants will complete the following at the point of site set up:

Short demographics questionnaire (age, gender, ethnicity, job role, grade, training).Mechanism of action questionnaire—an 11-item questionnaire measuring the extent to which the CHARMER intervention has addressed the intended four barriers and one enabler to proactive deprescribing.^15^Process of deprescribing questionnaire—a 19-item questionnaire capturing the extent to which practitioners undertake the steps within the process of proactively deprescribing in hospital.^18^

### Withdrawal

Hospitals, geriatricians and pharmacists and patient participants will be able to withdraw from the study at any time, without providing a reason, by informing a member of the research team. If a hospital chooses to withdraw from the trial, all data collected up until the point of withdrawal will be retained and a replacement site may be recruited.

If geriatrician and pharmacist participants choose to withdraw during the trial, any data they have already contributed as participants will continue to be used. If it is feasible and the trial can progress as planned, we will work with the relevant PI to recruit a replacement geriatrician or pharmacist if one withdraws. If this is not possible, for example, study is nearing completion, we will continue the trial with the remaining geriatricians and pharmacists.

Where patients choose to withdraw, although not obliged to give a reason, a reasonable effort will be made to establish this reason, while remaining fully respectful of the participant’s rights. All study data collected up to the point of withdrawal will be retained.

### Internal pilot

An internal pilot will be conducted with Step 1 hospitals with the following stop/go criteria:

An average of 200 patients per hospital enrolled over 3 months (Green).An average of 150–199 patients per hospital enrolled over 3 months (Amber).Below an average of 150 patients per hospital enrolled over 3 months (Red).

If ‘Green’, the trial will proceed. ‘Amber’ it will proceed if appropriate solutions to improve recruitment are identified. ‘Red’ will require the Trial Steering Committee to make a decision regarding whether to proceed.

### Participant timeline

Hospitals will participate in the trial from month 0 to month 21. Hospitals will be required to identify a PI responsible for local trial delivery and project manager for intervention implementation. Geriatricians and pharmacists will participate during the intervention implementation period until trial completion.

All patients admitted to the study wards under the care of a participating geriatrician will be enrolled, with permission from the national Confidentiality Advisory Group (CAG), for inclusion of their routinely collected data. This is unless they have notified the NHS in advance of a desire to be excluded from all research activity.

Figure 1 shows how patients will be enrolled into the trial, separating out control, implementation and intervention periods. The implementation phase is the point at which the intervention is delivered to the participating doctors and pharmacists, such that post-implementation, the intervention can be delivered.

During ‘enhanced data collection periods’, patients consenting to participation on a study ward under the care of participating geriatricians will be participants from the time of admission until 3 months post-discharge. We will notify the consented patient’s primary care medical practice by letter of their participation.

### Site set up

We will provide the Project Manager and PI with a CHARMER intervention implementation handbook, developed for the feasibility study and subsequently refined.^15^ A CHARMER trial handbook, comprising instructions regarding delivering the trial and CHARMER intervention in accordance with the approved research ethics and governance processes, will be provided to the PI.

The site will be expected to conduct the trial in compliance with the approved research protocol. The PI or their delegate will be required to document and explain any deviation from the approved protocol and communicate this to the study team at NCTU.

### Sample size

The underpinning feasibility study showed that recruitment to an original planned cluster randomised trial would require recruitment of over 40 hospitals and was unlikely to be achieved. Consequently, the design was changed to a stepped wedge due to the increased power provided by this design.

With a baseline step with all hospitals receiving the control followed by four separate steps, each randomising five hospitals to switch from control to intervention (20 hospitals in total) will have 89.5% power to detect a difference of 16.7% to 13.7% of 90-day re-admission rates assuming a 5% level of significance and an intra-class correlation coefficient (ICC) of 0.05 and 200 participants per hospital per step. The total sample size will be 20 000 participants. The anticipated 3% difference is similar, but slightly smaller, to the difference reported in the MedSafer study.^19^

From our feasibility study findings, we estimate that 10% of patients on study wards or consultees will provide written (or, if required, virtual) informed consent for additional patient-reported outcome data. For the enhanced data collection period, where medication changes are recorded in hospital, then if the sites collect data on 60 participants in each of the enhanced data collection periods, the study will have 99.99% power to detect an average change of 0.5 medications between the control and intervention phase, assuming a SD of 1.5 medications, a 5% level of significance and an ICC of 0.05.

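### The 89.5% power is for a five-period direct switch and omits the 3-month implementation quarter; for the six-quarter design described, power depends on how that quarter is analysed

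*Protocol article*

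**What the plan says.** The Sample size section builds its calculation as follows: "With a baseline step with all hospitals receiving the control followed by four separate steps". Five hospitals switch at each step, with 200 participants per hospital per step, an ICC of 0.05 and a 5% significance level. For this layout the section states "20 hospitals in total) will have 89.5% power to detect a difference of 16.7% to 13.7% of 90-day re-admission rates", with a total of 20 000 participants. The Abstract repeats the claim: "the study will have 89.5% power at 5% significance level". Neither place mentions an implementation phase.

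The Trial design section does. It says that the implementation phase "will last for 3 months for all hospitals, prior to transferring into the active intervention phase", and then "Each site will therefore take part in the trial for a total of 18 months". The Participant timeline section separates control, implementation and intervention periods and places delivery of the intervention after implementation. The Recruitment section gives a window of 1 February 2024 to 31 July 2025, which is also 18 months.

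The Main effectiveness analysis section specifies a logistic mixed model with hospital as a random effect and arm and time period as fixed factors, on all patients. It does not say how patients admitted in the implementation quarter are classified.

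**The concern.** Eighteen months in 3-month steps is six quarters, not five, and one of each hospital's six is spent in implementation. With C for control, I for implementation and T for active intervention, the four groups follow:

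- Group 1: C I T T T T
- Group 2: C C I T T T
- Group 3: C C C I T T
- Group 4: C C C C I T

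Control and active hospitals are observed at the same time only in quarters 3 and 4. Quarters 1 and 2 contain no active hospital, and quarters 5 and 6 contain no control hospital. Because the model adjusts for time period, most of the information on the effect comes from such concurrent comparisons, so an unclassified quarter between control and active phases can cost a good deal of power.

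The figure carries weight. The article justifies moving from a cluster randomised trial, with half the number of hospitals, by the power of the stepped wedge. A null result would also be read as coming from a trial with about 90% power.

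**Working it through.** **Inputs (Sample size section).** Rates 16.7% and 13.7%, difference 0.03; 20 hospitals in four groups of five; m = 200 per hospital per period; ICC 0.05; alpha 0.05, taken as two-sided because that reproduces the stated figure.

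**Method.** Generalised least squares on hospital-by-period means, with a hospital random intercept and fixed period effects, the linear counterpart of the planned model. With total variance s2, each hospital has covariance V = 0.05 × s2 × J + (0.95 × s2 / m) × I, where J is a matrix of ones and I the identity. The variance of the effect is its diagonal element of the inverse of the sum over hospitals of D'V⁻¹D, where D holds the period and treatment indicators. Power = Φ(0.03/SE − 1.96).

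**Variance.** At the control rate, s2 = 0.167 × 0.833 = 0.1391, so the between-hospital part is 0.05 × 0.1391 = 0.00696 and the within-hospital part is 0.95 × 0.1391 / 200 = 0.000661. A second convention averages the variances at the two rates.

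**Step 1: the plan's own figure.** Five periods, direct switch, control-rate variance: SE = 0.00933, and Φ(0.03/0.00933 − 1.96) = 89.54%. This matches the stated 89.5%. The averaged variance gives 91.7%.

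**Step 2: the six-quarter layout at 200 per quarter.**

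| Handling of the implementation quarter | Power, control-rate variance | Power, averaged variance |
|---|---|---|
| Excluded from the contrast | 68.1% (SE 0.01235) | 71.4% (SE 0.01188) |
| Kept, with its own term | 71.1% (SE 0.01192) | 74.4% (SE 0.01147) |
| Coded control, no effect yet; or coded intervention, full effect | 92.3% (SE 0.00887) | 94.0% (SE 0.00853) |
| Coded either way, half the effect present | 46.5% | 49.5% |
| Coded control, full effect; or coded intervention, no effect | about 7% | about 7% |

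In the last two rows the estimate is biased towards zero: its expected value falls from 3.0 points to 1.7 at half effect and to 0.3 when the coding is fully wrong. The 7% counts both tails.

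With exclusion, the effect variance is (0.01235/0.00933)² = 1.75 times that of the five-period layout. The difference detectable with 89.5% power is (1.960 + 1.254) × SE: 4.0 points with SE 0.01235, 3.8 points with SE 0.01188.

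**Step 3: higher throughput.** The hospital eligibility criteria mention about 100 patients a month, so 3 × 100 = 300 a quarter. Power is then 84.4-87.0% with exclusion and 86.7-89.2% with a separate term.

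**Step 4: the total.** 20 × 5 × 200 = 20 000 fits the five-period layout. It also fits six quarters less one per hospital: 20 × 6 × 200 − 20 × 200 = 20 000. Using all six quarters would give 24 000.

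**The case against.** A reader might infer that the trial as described simply has 68% power. The documents do not support that. The figure requires implementation-quarter patients to be left out of the contrast, and no section says so. The Main effectiveness analysis section specifies intention-to-treat with data from all patients, and the data collection section describes the full 18 months as control and intervention steps. The total of 20 000 does not settle it, because it fits both the five-period layout and exclusion. This objection stands, and it is why the result is conditional.

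It does not rescue 89.5%. Keeping the quarter as control or as intervention preserves power only if the effect in that quarter is essentially absent or essentially complete. The Intervention description section points to something between: the action plan and workshops are delivered during implementation, while the briefings and benchmarking reports belong to the active phase. Even the favourable codings give 92-94%, not the printed figure.

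Two further objections have some force. Handling of transition patients is commonly left to the SAP, which is not shown and takes priority, so silence on it is not in itself an error. The error is a specific power figure for a layout that the article's own design section contradicts. Throughput may also exceed 200; at 300 the shortfall is small. But ward throughput of about 100 a month does not guarantee 300 enrolled, and the power statement uses 200.

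A reader might also want power printed beside the pilot limits, since Green is "An average of 200 patients per hospital enrolled over 3 months (Green". Those limits are enrolment criteria and make no power claim, so this is not required.

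**Conclusion.** The point holds in conditional form. The stated power was calculated for a layout that the trial does not run. At the stated inputs the six-quarter design has about 68-71% power with the implementation quarter excluded and 71-74% with a separate term. Coding the quarter as control or as intervention makes power depend on an unknown partial effect, from 92-94% in the most favourable case to about 46-49% at half effect.

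These figures assume equal hospital-period sizes, a within-hospital correlation that is constant over time, a normal approximation on the risk-difference scale and a two-sided 5% test. The ranges span the control-rate and averaged variances; applying either variance as the within-hospital variance, or using the intervention-rate variance, widens the exclusion figure to 66-75%. That the effect in the implementation quarter is partial is suggested by the timing of the components, not stated.

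This should be corrected, because the figure supports the choice of design and the correction is cheap.

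**What to change.** 1. State in the primary analysis that patients admitted in a hospital's implementation quarter are either excluded from the control-versus-intervention contrast or given their own model term.
2. Restate the power, in the Sample size section and the Abstract, for the six-quarter layout under that rule. At 200 per hospital per quarter it is about 68-71% (excluded) or 71-74% (own term); at about 300 it is 84-87% or 87-89%. Equivalently, with exclusion at 200, give a detectable difference of about 3.8-4.0 points at 89.5% power.
3. Say which quarters the total of 20 000 counts.

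The cost is recalculation and wording, and a less favourable stated power. No extra patients or hospitals are needed to make the correction.
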